#### Drop-out

2.5.1

Including patient self-withdrawal due to poor efficacy, intolerance, refusal to account, loss to follow-up, and doctor dissuasion due to poor adherence, comorbidities, specialties, adverse reactions, etc.

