#### Exclusion criteria

2.5.2

a Those who do not meet the inclusion criteria and are mistakenly included;

b Subjects with poor adherence, not following the designed treatment regimen strictly, or whose something would affect the observed results of the study during the trial;

c Subjects with incomplete information on various materials.

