### Sample size calculation

2.8

This randomized controlled study evaluates the effects of three methods on postmenopausal patients with OP. Bone mineral density (BMD), McGill Pain Questionnaire Short-Form (SF-MPQ), Osteoporosis Symptom Score (OSS), Mini-Mental State Examination (MMSE), and Beck Depression Inventory-II (BDI-II), serum leptin, leptin receptor, norepinephrine level will be used as evaluation indicators. According to the preliminary test data, it was calculated that after treatment, the SF-MPQ score (PRI total score) in the CEA group decreased by 17.23 ± 2.84, that in the rTMS group decreased by 16.41 ± 1.77, and that in the CEA combined with rTMS group decreased by 17.40 ± 2.17. The two-sided test value α = 0.05 was used. Test power 1-β = 0.95. Using G*Power3.1.9.7 software and single factor analysis of variance in the F test (27, 28), the required sample size of n = 87 cases was calculated, and the shedding rate was set at 10%. The total sample size was 96 cases, and the required sample size for each group was 32 cases.

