#### Study schedule

2.9.1

Baseline information on age, menopause age, weight, education, vital signs, and duration of illness will be collected and recorded (Table 1). Then, the primary outcomes will be the changes in BMD scores and total efficiency of Chinese Medicine Symptoms before and after treatment. Secondary outcomes will include the SF-MPQ, OSS, MMSE, and BDI-II every 4 weeks for 12 weeks of treatment and 8 weeks follow-up period. Adverse events that occur during the trial will be recorded. The leptin, leptin receptor, and norepinephrine levels of peripheral blood must be measured before and after treatment.

**Table 1 tab1:** Trial flow and schedule: enrollment, interventions, and assessments.

Research stage			Duration of treatment (weeks)				Follow-up period (weeks)	
Inclusion/exclusion criteria			0	4	8	12	4	8
Sign the informed consent form			√					
		General information	√	√	√	√		
		Previous medical history	√					
		Clinical symptoms and physical signs	√	√	√	√		
Physical examination		Tongue manifestation, pulse, manifestation, weight	√			√		
		Vital signs: T, BP, P, R.	√			√		
Security check		Electrocardiogram	√			√		
		Liver function	√			√		
		Renal function	√			√		
		Blood lipids	√			√		
Intervention		CEA						
		rTMS						
		CEA combined with rTMS						
Efficacy indicators	Primary outcome	①BMD	√			√			②Total efficiency of Chinese Medicine Symptoms	√			√		
		③SF-MPQ	√	√	√	√	√	√
		④OSS	√	√	√	√	√	√
	Secondary outcome	⑤Leptin	√			√		
		⑥Norepinephrine	√			√		
		⑦Leptin receptor	√			√		
		⑧MMSE	√	√	√	√	√	√
		⑨BDI-II	√	√	√	√	√	√
Blood sample collection			√			√		
Randomization			√					
General assessment	Clinical efficacy					√		
	Compliance assessment		√	√	√	√		
	Adverse event		√	√	√	√		
	Safety evaluation		√			√		

T, Temperature; BP, Blood Pressure; P, Pulse; R, Respiration; CEA, Catgut Embedding in Acupoints; rTMS, repetitive Transcranial Magnetic Stimulation; BMD, Bone Mineral Density; SF-MPQ, McGill Pain Questionnaire Short-Form; OSS, Osteoporosis Symptom Score; MMSE, Mini-Mental State Examination; BDI-II, Beck Depression Inventory-II.

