#### Clinical manifestation

2.11.1

SF-MPQ and OSS will be measured every four weeks for 5 months. All evaluation indicators will be assessed at six time points: baseline, mid-treatment (4 and 8 weeks of treatment), post-treatment (12 weeks), and 1 month and 2 months after the treatments.

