### Statistical analysis

2.14

The data will be recorded and checked for accuracy, and the data related to baseline and clinical symptoms will be statistically analyzed using SPSS 27.0 software. The *t*-test will be performed for customarily distributed measures that meet the chi-squared test, and the *t′*test will be conducted for standards that meet the normal distribution but do not meet the chi-squared test. Independent sample *t*-tests are used between two groups, and paired sample *t*-tests will be used for pre-treatment and post-treatment comparisons within groups. Non-normally distributed measures are described by “median (interquartile range)” [*M (IQR)*], and non-parametric tests will be performed. *The Mann–Whitney U* test will compare two independent samples, and the *Wilcoxon Z* test will be used for pre-and post-treatment-comparisons. The scale scores at more than three of these time points are compared using repeated measures *ANOVA*. Correlations will be expressed as correlation coefficients (*r*). Correlations between the two measurement variables will be analyzed by Pearson correlation analysis if they conform to a normal distribution and Spearman analysis if they do not obey a normal distribution. Given that our study defines two primary outcomes, a Bonferroni correction will be applied, thus adjusting the significance level for individual outcome analyzes to *α*/2 to control the overall type I error rate, setting *α* = 0.05 (39).

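### Repeated measures ANOVA over six visits drops partly observed participants from the over-time comparison of the secondary scales; a mixed model would keep them

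*Protocol article*

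**What the plan says.** Section 2.14 (Statistical analysis) fixes the method for the scales: "The scale scores at more than three of these time points are compared using repeated measures" ANOVA. It also says that the data "will be statistically analyzed using SPSS 27.0 software". The same section names independent-sample t-tests (or Mann–Whitney) between two groups and paired tests (or Wilcoxon) for before-and-after comparisons.

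The schedule is in section 2.9.1: "Secondary outcomes will include the SF-MPQ, OSS, MMSE, and BDI-II every 4 weeks for 12 weeks of treatment and 8 weeks follow-up period". Section 2.11.1 confirms the count for the clinical scales: "All evaluation indicators will be assessed at six time points", namely baseline, weeks 4, 8 and 12, and one and two months after treatment.

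On loss, section 2.8 says that "the shedding rate was set at 10" per cent. Section 2.5.1 counts as drop-out "patient self-withdrawal due to poor efficacy, intolerance, refusal to account, loss to follow-up", among other reasons. Section 2.5.2(c) lists for exclusion "Subjects with incomplete information on various materials", and 2.5.2(b) lists poor adherence. The protocol names no imputation, no mixed model and no intention-to-treat set.

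**The concern.** Classical repeated measures ANOVA needs a value at every visit entered. If nothing is imputed, one missing visit removes a participant's whole record on that scale from the over-time comparison. If all six visits are entered, a woman seen at weeks 0, 4, 8 and 12 who misses only the last follow-up visit also drops out of the on-treatment part of that comparison.

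The protocol expects some loss to be related to outcome, since poor efficacy and intolerance are listed reasons for leaving. It also expects loss during follow-up, where the last two scale visits fall. The arms carry different burdens: 12 CEA sessions, 36 rTMS sessions, or both. Unequal loss is therefore possible, though the protocol does not predict it. What is at stake is the comparison of pain, symptoms, cognition and mood over time. SF-MPQ is also the scale on which the sample size was calculated.

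**Working it through.** **Which outcomes.** Four scales have six visits: SF-MPQ, OSS, MMSE and BDI-II. The abstract and the text of section 2.9.1 call them secondary. BMD and total efficiency are assessed only before and after treatment, so the ANOVA sentence does not reach them.

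**How many are lost (section 2.8).** 96 × 0.90 = 86.4, close to the stated 87, so the planned 10% is already in the sample size. Further loss needs an assumed rate q of missed visits among those who stay. The share with all six values is 0.9 × (1 − q)^5:
- q = 2%: 0.9 × 0.98^5 = 0.814, or 78 of 96.
- q = 3%: 0.9 × 0.97^5 = 0.773, or 74 of 96.

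The protocol gives no value for q.

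**Bias in the arm contrast.** Assumptions: no true arm difference, 32 per arm, score SD 1 at each visit, correlation 0.6 between visits, and the k poorest week-8 responders in an arm withdraw.
- Variance of a change from baseline: 2 × (1 − 0.6) = 0.8, so its SD is 0.894.
- Covariance of week-8 and week-12 change: 1 − 0.6 = 0.4, so their correlation is 0.4/0.8 = 0.5.
- Shift in the completers' mean week-12 change: 0.5 × 0.894 × S(k)/(32 − k), where S(k) is the expected sum of the k largest of 32 standard normal values.

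| k | S(k) | Shift (SD) |
|---|---|---|
| 0 | 0 | 0 |
| 1 | 2.07 | 0.030 |
| 2 | 3.72 | 0.055 |
| 3 | 5.12 | 0.079 |
| 4 | 6.33 | 0.101 |
| 5 | 7.40 | 0.123 |
| 6 | 8.34 | 0.143 |

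The between-arm bias is the difference of two shifts:
- 3 vs 3: 0.
- 2 vs 4: 0.101 − 0.055 = 0.046 (simulated 0.04).
- 1 vs 5: 0.123 − 0.030 = 0.093 (simulated 0.08 to 0.10).
- 0 vs 6: 0.143 (simulated 0.14).

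The standard error of the contrast is about √(0.8 × (1/31 + 1/27)) = 0.235 SD for 1 vs 5 and about the same for 0 vs 6. The bias in these two cases is thus roughly 0.4 and 0.6 standard errors. A likelihood estimate on all available visits was within 0.01 SD of zero in simulation.

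**If withdrawal depends on the unseen week-12 response.** The factor 0.5 drops out, so the complete-case bias is about twice as large: 0.19 SD (1 vs 5) and about 0.28 SD (0 vs 6). The likelihood estimate is then biased too, by 0.13 and 0.19 SD.

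**Within-arm change on the SF-MPQ scale.** The pooled SD from section 2.8 is √((2.84² + 1.77² + 2.17²)/3) = 2.30. If the 3 poorest final responders of 32 are lost, the mean decrease rises by 2.30 × 5.12/29 = 0.41 points. With that loss in every arm, the planned combined-minus-rTMS difference stays at 17.40 − 16.41 = 0.99. With 5 lost from rTMS and 3 from the combined arm, it becomes 0.99 + 0.41 − 2.30 × 7.40/27 = 0.99 + 0.41 − 0.63 = 0.77.

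**The case against.** The protocol names the test and does not state complete-case deletion. An analysis plan that is not shown could impute first, and repeated measures ANOVA on imputed data would satisfy the sentence. This stands as a caveat. Yet the published text that bears on the matter fits a completer analysis: 2.5.2(c) lists incomplete information for exclusion, and the trial is sized on 87 remaining after loss. The choice of test is itself stated, so this is not merely absent detail.

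A reader might infer that drop-outs have no place in any analysis. The documents do not support that. The two-sample and paired tests in 2.14 need only the values compared, so a woman with scores at weeks 0 and 12 can enter them. Also, more than three time points need not mean all six. If only the four visits up to week 12 are entered, missing a follow-up visit costs her nothing there.

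A reader might also infer that outcome-related loss always biases the arm comparison, or that the usable number must fall below 87. Bias in the contrast needs loss that works differently by arm, and at 3 vs 3 withdrawals it is zero. The protocol uses a single 10% figure and gives no arm-specific rates. The 78 and 74 rest on assumed missed visits added to a loss already budgeted. Whether 87 is adequate is a separate question, so falling below it proves little here.

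Finally, the loss of precision from withdrawal alone is negligible at the planned rate: at 3 vs 3, the simulated standard error was 0.224 SD for complete cases and 0.221 for the likelihood estimate.

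**Conclusion.** The point holds in limited form. Unless data are imputed, the named test leaves partly observed participants out of the over-time comparison of four secondary scales. With equal loss across arms, the costs are discarded scores and inflated within-arm change (0.08 SD at week 12 for 3 of 32 lost, under the assumptions above). With unequal loss, the contrast is biased towards the arm that loses more poor responders, from about 0.04 SD (2 vs 4) to 0.14 SD (0 vs 6). These sizes rest on an assumed correlation of 0.6 and on withdrawal driven by week-8 response. The split of withdrawals between arms is also assumed. The two primary outcomes are untouched. A better method is available in the same software, so the change is worth making, but nothing here shows that the planned comparison is invalid.

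**What to change.** In section 2.14, replace the repeated measures ANOVA sentence with text to this effect: SF-MPQ, OSS, MMSE and BDI-II will each be analysed with a linear mixed model for repeated measures (SPSS MIXED, unstructured covariance) containing baseline score, arm, visit and arm-by-visit, using all available visits of all randomised participants. The named contrasts are combined vs CEA and combined vs rTMS at week 12, and the follow-up visits are reported from the same model.

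Also state that incomplete data or poor adherence under 2.5.2(b) and (c) does not remove a participant from this analysis. Otherwise the two sections contradict each other.

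The cost is two short edits. No new data or software are needed, and the trial was still recruiting when the protocol was published. There are two downsides. An unstructured covariance over several visits uses more parameters in a trial of 96. The model also removes bias only when dropout depends on observed scores. Where it depends on unobserved ones, the bias is reduced (0.13 against 0.19 SD for 1 vs 5) but not removed, so a sensitivity analysis for that case would be a sensible addition.

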### Design and study setting

2.1

A total of 96 participants meeting the diagnostic criteria for PMOP according to the guidelines of the clinical trial committee will be recruited at Bao’an Hospital of Traditional Chinese Medicine. Subjects will be informed of every study detail and sign an informed consent form.

This randomized, controlled clinical trial comprises three parallel groups. It compares the effectiveness of the individualized CEA group, CEA combined with the rTMS group and rTMS groups (Figure 1).

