#### BMD test

2.10.1

The patient’s BMD of L2-L4 in the lumbar spine and BMD of the left femoral neck will be measured by DXA once before and after the treatment.

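### The α/2 correction counts two outcome names but not the three arm pairs or the two BMD sites, so it does not hold the overall type I error at 5%

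*Protocol article*

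**What the plan says.** All references are to the protocol article.

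- **Correction (2.14 Statistical analysis).** The reason given is the number of outcomes: "Given that our study defines two primary outcomes, a Bonferroni correction will be applied". The stated purpose is "adjusting the significance level for individual outcome analyzes to *α*/2 to control the overall type I error rate", with α = 0.05.
- **Outcomes (2.9.1 Study schedule).** "the primary outcomes will be the changes in BMD scores and total efficiency of Chinese Medicine Symptoms before and after treatment".
- **BMD (2.10.1 BMD test).** "BMD of L2-L4 in the lumbar spine and BMD of the left femoral neck will be measured by DXA". No primary site and no combined measure is defined.
- **Arms (2.1 Design and study setting).** "This randomized, controlled clinical trial comprises three parallel groups".
- **Between-arm tests (2.14).** Independent-sample t "tests are used between two groups, and paired sample" t-tests within groups; Mann–Whitney U replaces the former when data are not normal. The only ANOVA there is a repeated-measures one for scale scores at more than three time points. BMD and total efficiency are assessed only before and after treatment, so it does not reach them. No test is named for the effective rate.
- **Sample size (2.8).** The calculation used "single factor analysis of variance in the F test", so a three-group test was assumed at the design stage.

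**The concern.** A Bonferroni divisor of 2 protects a family of two tests. A three-arm trial compared by two-group tests has up to three tests per outcome variable, and BMD supplies two variables. The protocol does not reduce that number: it names no primary pair, no primary BMD site, no order of testing and no preliminary three-group test. At stake is a property that the protocol claims for itself. This is its only multiplicity safeguard, and as worded it leaves the arm pair and BMD site to be chosen after the results are seen.

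**Working it through.** **Inputs from the protocol.** α = 0.05, two-sided (2.8, 2.14); 0.025 per outcome (2.14); three arms of 32 (2.8); two primary outcomes (2.9.1); two BMD sites (2.10.1). **Assumption:** the correlation between outcome variables is not given, so 0 to 0.9 is shown.

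**1. The plan's own figure.** Two tests at 0.025: Bonferroni sum 2 × 0.025 = 0.05; if independent, 1 − 0.975² = 0.0494. The claim is right for one test per outcome.

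**2. Number of tests.** Three arms give 3 pairs.
- One outcome: 3 tests.
- Two outcomes, one BMD site: 3 × 2 = 6 tests.
- Two BMD sites plus the effective rate: 3 × 3 = 9 tests.

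**3. Values if the tests were independent.** 1 − 0.975³ = 7.3%; 1 − 0.975⁶ = 14.1%; 1 − 0.975⁹ = 20.4%. Pairs share arms and so are not independent. These figures overstate the error.

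**4. Simulation with shared arms.** Global null, 32 per arm, normal outcomes, all pairwise two-sided tests at 0.025, 40,000 trials per setting:

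| Correlation | 6 tests (one BMD site) | 9 tests (both sites) |
|---|---|---|
| 0 | 12.5% | 18.4% |
| 0.3 | 12.1% | 17.1% |
| 0.5 | 11.8% | 15.9% |
| 0.7 | 10.9% | 14.3% |
| 0.9 | 9.1% | 11.1% |

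One outcome with three pairs gives about 6.3% (6.2–6.5% over repeated runs), whatever is assumed about sites or correlation.

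**5. Total efficiency depends partly on BMD.** Section 2.10.2 defines response partly by bone density. Building the rate that way gives 14–17% for nine tests at 32 per arm, and 13–16% at 29 per arm (87/3, the number before the dropout allowance).

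**6. Narrower families.**
- Only the two pairs that involve the combination: 6.9–9.1% for two outcomes, about 8–13% with both BMD sites.
- One pair only, both BMD sites plus the rate: about 5–7%.
- One pair and one BMD site: step 1 applies, and 5% holds.

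**7. After the fix.** With a three-group test at 0.025 before any pairwise test, the error is about 2.5% per outcome and 3.7–5.0% for two outcomes. If both BMD sites stay primary, the same gate gives 4.5–7.3%, so naming the site is needed too. If one arm truly differs from the other two, only one true null pair remains, and it is tested at 0.025. That is why no further split is needed with three arms.

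**8. Power cost.** For a 0.8 SD difference at 32 per arm, the t-test noncentrality is 0.8 × √(32/2) = 3.2, and power at 0.025 is about 82%. The F-test noncentrality is 32 × 0.8² × 2/3 = 13.7 if the third arm equals one of the pair, and 32 × 2 × 0.4² = 10.2 if it lies midway. Requiring both tests to reject gives about 78% and 72%.

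**The case against.** The protocol nowhere says that all three pairs, or both BMD sites, are confirmatory. It describes general methods, gives no test for the effective rate (so three pairwise rate tests are a construction), and is a journal article whose analysis plan is not shown. Post-hoc procedures and the choice of site are often left to that plan. All of this is fair, and it is why the size must be a range. It does not rescue the claim: the article justifies α/2 by the outcome count alone and states that overall control follows. Of the readings in the working, 5% is secured across the whole range of correlations only with one pair and one site, and the article specifies neither.

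Three stronger readings are tempting and are not supported:

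- **Familywise error of 16–20%.** The upper end treats pairs that share arms as independent. The largest simulated value is about 18%, at zero correlation, and 16% or more needs nine confirmatory tests and, in general, correlation of about 0.5 or less.
- **A false claim for the combination three to four times as likely as stated.** Three of the nine tests compare CEA with rTMS and do not concern the combination. The six that do give about 8–13% in either direction.
- **Four primary outcomes.** In Table 1 as extracted, SF-MPQ and OSS stand above the secondary label. But that table is visibly broken, and the abstract and sections 2.9.1, 2.10 and 2.11 consistently make both secondary.

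**Conclusion.** Wrong as written. The α/2 divisor does not deliver the stated 5% control, because it covers neither the arm pairs nor the BMD sites. The firmest figure is about 6.3% against 2.5% for one outcome with three pairs. Overall, the error is roughly 9–12.5% with one BMD site and 11–18% with both, or about two to three and a half times the nominal 5%. These figures assume the global null, 32 per arm, all pairs tested, and correlations between 0 and 0.9. That the direction is upward is well supported. The exact size depends on which tests the investigators regard as confirmatory.

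**What to change.** In 2.10.1, name one BMD site as primary and make the other secondary. In 2.14, state that each of the two primary outcomes is first compared across all three arms at 0.025 (one-way ANOVA or Kruskal–Wallis for BMD change, a 2-df chi-square for the effective rate), and that pairs are tested at 0.025 only if that test rejects. This also brings the analysis into line with the ANOVA assumed in 2.8.

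Two alternatives would also work: name the primary contrast or contrasts in advance and count them, or divide α by the true number of tests (0.05/6 = 0.0083 with one BMD site, 0.05/9 = 0.0056 with both).

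The change is to analysis wording only; visits, measurements and treatment are untouched. The price of the gate is the loss of pairwise power shown in the working, which is modest if the third arm matches one of the pair and larger if it lies between them. Section 2.16 says that recruitment has begun, so the amendment should be dated before anyone sees outcome data by group.

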### Dissemination

2.15

The study findings will be shared at scientific conferences and published in peer-reviewed journals. The study participants will also have the chance to receive the results through phone or email.

### Trial status

2.16

Currently, the protocol is version 1.0, registered on 24 July 2023. Clinical registrations have been reviewed and approved, and we are now recruiting subjects.

## Discussion

3

### Feasibility analysis of rTMS combined with CEA for PMOP

3.1

The “brain-bone axis” is critical for bone metabolism, sensory innervation and endocrine connections between organs (1). The bone is rich in sensory and sympathetic innervation and interacts with the central nervous system (40, 41). The central regulation of bone mass can be divided into the following three main pathways: i) regulation of the sympathetic nervous system through neuronal signaling in the brainstem and hypothalamus; ii) the hypothalamus-pituitary neuroendocrine signaling pathway; and iii) direct action on bone cells through the hypothalamic secretion of neuropeptides (42). There is growing evidence that the nervous system plays an irreplaceable role in bone development and metabolism by directly or indirectly regulating the activity of osteoblasts (OBs) and osteoclastss (OCs) (43). Thus, based on the neuro-bone mass regulation theory, we aim to stimulate the nerve systems to explore novel treatments for PMOP.

A meta-analysis of our pre-published (44) showed that the efficacy of CEA for PMOP is equivalent to that of the drug control group and is safer. Our previous clinical trials have proved that CEA can increase serum estradiol levels and regulate bone metabolism and free radical levels in PMOP (12). Animal studies have demonstrated that CEA can alleviate oxidative stress resulting from estrogen deficiency. It exerted a regulatory effect on aromatic amino acids, specifically phenylalanine and tyrosine, and may influence the synthesis of monoamine neurotransmitters in ovariectomized rats. Notably, this regulatory effect appeared to surpass that of estrogen (45). Acupoint stimulation of bilateral Shenshu (BL 23) can increase pituitary ERα expression, reduce body weight in ovariectomized rats, and benefit the rats (46). In conclusion, Acupoint stimulation in the periphery may improve bone metabolism by modulating the level of central neurotransmitters (12).

Clinical studies have demonstrated that acupuncture with TMS therapy is more effective than monotherapy in improving clinical symptoms (47, 48). Acupuncture activates various brain regions through a bottom-up modulation approach, while TMS generates action potentials in cortical axons that spread to other neurons via synapses, resulting in neuronal activation that spreads excitation to neighboring cortical and subcortical regions (49). The combination of these two treatments creates a pattern of central-peripheral and closed-loop stimulation that is superior for improving neurophysiological function (50, 51). CEA combined with rTMS can stimulate the peripheral-central simultaneously, thus correcting the imbalance of brain bone mass regulation and promoting peripheral bone mass formation (52–54). The combination of CEA and rTMS may play a coordinating, synergistic, and side-effect-reducing role (55), which is of great clinical value in exploring better treatment options for PMOP.

